#### Follow-up – T1

A year after standard treatment completion, patient will once again benefit from CGA and sarcopenia assessment as described for T0.

Total duration of study will be 48 months, recruitment period will be 24 months and patient follow-up period, 12 months. A year after ADT end, patient will be contacted either by the geriatrician or the study coordinator to schedule the follow-up (T1). The study procedure and data collection are detailed in Table 1.

**Table 1 Tab1:** HoSAGE Study schedule of activities and procedures

	T0	Treatment phase	T1
Oncologist consultation	X	X	
Diagnosis	X		
G8 score ≤14	X		
Geriatrician consultation	X		X
Enlighten consent	X		X
Enrollment	X		X
CGA	X		X
Demographic information	X		X
Social isolation	X		X
Cognitive status (MMSE and clock drawing test)	X		X
Mood status (GDS)	X		X
Autonomy (ADL and IADL Score)	X		X
Nutritional status (BMI, MNA score and Albumin)	X		X
Mobility (OLGT, Gait speed)	X		X
Sarcopenia screening (SARC-F, Handgrip test and chair stand test)	X		X
If Sarcopenia risk suspected (SARC-F≥4/10), and Muscle strength is impaired, SMI will be measured by (DXA)^a^	X^a^		X^a^
Radiotherapy treatment (dates, dose delivered and number of fractions)		X	
Androgen deprivation therapy (dates, dose delivered, frequency, adverse events)		X	

^a^DXA assessment performed only if SARC-F score is ≥4/10 and muscle strength is impaired (either handgrip strength under 27 kg for men and 16kg for women or five chair stand test is performed in more than 15 seconds)

*CGA: Comprehensive Geriatric Assessment; MMSE: Mini Mental State Examination; GDS: Geriatric Depression Scale; ADL: Activity of Daily Living; IADL: Instrumental Activity of Daily Living; BMI: Body Mass Index; MNA: Mini Nutritional Assessment; OLGT: One Leg Balance Test; SARC-F: Strength, Assistance walking, Rise from a chair, Climb stairs, and Falls; SMI: Skeletal Muscle Index (appendicular muscular mass/seize*^*2*^*); DXA: Dual-energy X-ray*

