### Endpoints/Evaluation criteria

#### Primary endpoint

The primary endpoint is:The evaluation of sarcopenia prevalence for patients 70 years and older with localized or locally advanced prostate cancer before treatment initiation.

The geriatrician will screen for suspicion of sarcopenia using the SARC-F questionnaire and muscle strength assessment as recommended by the EWGSOP2 guidelines [10]. Patient whose SARC-F score is superior or equal to four out of ten are at risk of sarcopenia and will undergo muscle strength assessment. Patient with impaired muscle strength (either handgrip strength under 27 kg for men and 16kg for women or five chair stand in more than 15 seconds) are considered with probable sarcopenia [10]. To ascertain sarcopenia diagnosis, SMI will be estimated using the Appendicular Skeletal Muscle Mass (ASMM) measured with dual-energy X-ray absorptiometry (DXA) [17], adjusted for body size (ASMM/height^2^). Chosen cut-off point for low SMI indicating sarcopenia diagnosis as per EWGSOP2 guidelines is <7.0 kg/m2 [10]. Sarcopenia severity will be evaluated using Timed up and Go test and Gait speed assessment.

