#### Secondary endpoints

The secondary endpoints are:The evaluation of sarcopenia incidence in patients 70 years and older with localized or locally advanced prostate cancer a year after the end of ADT. Sarcopenia assessment will be lead at enrollment and a year after ADT end.Evaluate the evolution of the physical performances by the measurement of mobility (Timed Up and Go test, gait speed and chair stand test) at enrollment and after ADT in patients 70 years and older with localized or locally advanced prostate.Evaluate quality of life (QoL) evolution before and after ADT for patient 70 years and older with localized or locally advanced prostate with or without sarcopenia. QoL will be evaluated using EORTC QLQ-c30 questionnaires and ELD-14 module at enrollment and a year after ADT end.Evaluate impact of socio-behavioral, anthropological and geriatric factors on sarcopenia prevalence for patients 70 years and older with localized or locally advanced prostate and on its incidence after ADT. Geriatric factors such as Autonomy (score <6 on Activity of Daily Living (ADL) Scale and score <4 on Instrumental Activity of Daily Living (IADL) scale) [18], nutrition (Weight, Body Mass index (BMI), Albumin, Mini Nutritional Assessment (MNA) )[19]., cognitive status (Mini Mental State Examination (MMSE)) [16], mood (Geriatric Depression Scale (GDS)) [20], polypharmacy, and comorbidities will be assessed by CGA. Demographic information such as age, gender, presence of a caregiver, urban or countryside way of living and physical activity (number of days when patient exercise an hour at least).Evaluate impact of ADT of patients 70 years and older with localized or locally advanced prostate on sarcopenia. Oncological data such as cancer stage and anatomy; testosterone and PSA levels at enrollment and a year after ADT end; treatment protocol for radiotherapy and ADT will also be collected.

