#### Data analysis

The data will be analyzed using SPSS version 17.0 software. Method and analysis will be based on the Consolidated Standards Of Reporting Trials Statement (CONSORT) (http://www.consort-statement.org/consort-statement/). The patients who would be inappropriately included despite providing consent and patients who removed their consent to participate won’t be included in the final analysis. The full population (including all subjects who will be enrolled and will be at least evaluated at T0) will be included in the analysis of primary endpoint. The normality of the parameters will be estimated using frequency histograms and the Shapiro test; the baseline parameters will be presented according to the timeline of assessments: ‘Enrollment – T0’ and ‘A year after ADT end – T1’.

The SMI under 7 kg/m^2^ at enrollment and /or a year after ADT end is considered as a proven sarcopenia diagnosis. Along with incidence of sarcopenia, we will monitor evolution of SMI and/or of physical performances (handgrip strength and/or chair stand test) for diagnosed sarcopenic patient. Only patients with probable sarcopenia (SARC-F score ≥4/10 and then muscle strength impairment), will benefit from a DXA exam [10, 22, 23]. To evaluate incidence, enrollment (T0) will be considered as baseline and compared to T1 data. Changes between initial SMI and/or handgrip strength and/or chair stand test will be compared between the two groups, and the analysis of variance for repeated measurements will be performed to compare the changes in the scores over time between the 2 groups. Multivariate analysis using linear regression models will be performed to determine the association between our analyzed variables and sarcopenia occurrence. Variables relevant to the models will be selected based on their clinical significance (two-tailed with 5% significance level). The secondary endpoints will be compared for all the patients between the 2 assessments (Chi2 test or Fisher’s exact test for categorical variables and Student’s t test for continuous variables).

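### The two-group test of change in SMI, handgrip and chair stand has no defined groups, uses SMI data selected on the outcome, and is biased for strength if the groups are sarcopenia status

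*Protocol article*

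**What the plan says.** The Data analysis section names the variables, the contrast and the test. For the variables and the contrast it says: "Changes between initial SMI and/or handgrip strength and/or chair stand test will be compared between the two groups". The method it then gives for this is repeated-measures ANOVA, applied to the change in scores across the same unnamed groups. The article does not say what the groups are. The nearest two-way split is in the Secondary endpoints section, for quality of life only: patients "with localized or locally advanced prostate with or without sarcopenia".

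SMI comes only from DXA, which is restricted: "Only patients with probable sarcopenia (SARC-F score ≥4/10 and then muscle strength impairment), will benefit from a DXA exam". Footnote a of Table 1 repeats the rule, "DXA assessment performed only if SARC-F score is ≥4/10 and muscle strength is impaired", and is attached to both the T0 and the T1 column.

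Under Primary endpoint, impaired strength means "handgrip strength under 27 kg for men and 16kg for women or five chair stand in more than 15 seconds", and "Chosen cut-off point for low SMI indicating sarcopenia diagnosis as per EWGSOP2 guidelines is <7.0 kg/m2". The time at which status is fixed is left open: a low SMI "at enrollment and /or a year after ADT end is considered as a proven sarcopenia diagnosis".

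**The concern.** The article commits to a test that conflicts with its own measurement rules. A between-group comparison of SMI change needs SMI at both visits in both groups, but SMI is taken only in men who already look sarcopenic at that visit. If the groups are sarcopenic versus not, two of the three outcomes (handgrip and chair stand) are also entry criteria for one of the groups, and the third (SMI) is the confirming criterion.

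The group-by-time term could then be produced by selection alone. With T0 groups it would look as though sarcopenic men withstand ADT better. With T1 groups it would look as though ADT caused marked loss in new cases. The abstract lists the relation between ADT and sarcopenia incidence among the primary objectives, so either reading would bear on a main message of the study.

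**Working it through.** **1. The plan's own figure.** The only sizing figure is the 95% confidence interval width for prevalence with 200 patients, 0.115 to 0.131. Exact (Clopper-Pearson) intervals give 0.1153 at 40/200 and 0.1313 at 60/200, so it reproduces. It concerns T0 prevalence and says nothing about the group comparison.

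**2. Who has paired SMI.** This follows from the DXA rule alone, under any grouping.

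| Meets DXA rule at T0 | Meets it at T1 | SMI change |
|---|---|---|
| yes | yes | available |
| yes | no (SARC-F or strength improved) | no T1 SMI |
| no | yes (includes new cases) | no T0 SMI |
| no | no | none |

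Whether SMI change is observed therefore depends on how SARC-F and strength evolve.

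**3. Assumptions used to size the effect.** The documents give none of these inputs.
- Handgrip: mean 30 kg, SD 8 kg, T0–T1 correlation 0.7, 0.8 or 0.9.
- SMI: mean 6.9 kg/m², SD 1.0, T0–T1 correlation 0.95.
- SARC-F positive in 40, 60 or 80%, T0–T1 correlation 0.8.
- Cross-correlations: handgrip–SMI 0.4, handgrip–SARC-F −0.4, SMI–SARC-F −0.2.
- Multivariate normal, no true change, no dropout.
- Sarcopenic means SARC-F positive, handgrip below 27 kg and SMI below 7.0.

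The chair-stand route into impaired strength is not modelled. Simulated T0 prevalence is 14.7 to 23.2%, at and below the low end of the plan's 20 to 30%.

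**4. SMI result, per 200 patients.**
- DXA at T0 in 40 to 65; at both visits in 25 to 51.
- Paired SMI in 19 of 29 to 37 of 46 men sarcopenic at T0, but in only 6 of 171 to 13 of 154 of the others. All of the latter are probable cases with SMI of 7.0 or more.
- Of new cases at T1, 9 of 11 (82%) to 14 of 15 (93%) have no T0 SMI.
- Within the twice-scanned subset, the baseline cut at 7.0 alone gives mean changes of about +0.02 (sarcopenic) and −0.07 kg/m² (not), a spurious difference of about 0.09.

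**5. Strength, groups set at T0.** With two visits, the group-by-time test is a comparison of mean change. With no true change, a group whose T0 mean lies a distance D from the overall mean moves back by (1 − r) × D, where r is the T0–T1 correlation. Under the section 3 assumptions:

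| r | Spurious handgrip difference, sarcopenic minus rest | Rejection rate of a nominal 5% test |
|---|---|---|
| 0.7 | +2.0 to +2.7 kg | 40 to 76% |
| 0.8 | +1.4 to +1.8 kg | 28 to 58% |
| 0.9 | +0.7 to +0.9 kg | 16 to 32% |

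**6. Strength, groups set at T1.** Men newly sarcopenic at T1 show a false handgrip loss of 1.8 to 6.1 kg, against about 0 in men who are never cases. The sign is opposite to step 5.

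**7. Who has strength measured.** The Screening and enrollment section and the Primary endpoint section give strength testing after an impaired SARC-F. Table 1 lists handgrip and chair stand at T0 and T1 without that restriction. These statements conflict, and any analysis of strength change depends on which holds.

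**The case against.** The strongest objection is that the groups are not defined, so a bias that depends on their definition cannot be asserted outright. ADT lasts 6 to 36 months and the impact of ADT exposure is a stated objective, so the groups could be levels of exposure. Those are not built from handgrip or chair stand, and the regression-to-the-mean and circularity arguments would fall away. A full protocol or SAP may also hold the definition. This stands: the strength argument is conditional, and the absence of a definition from an article is not by itself the finding. It does not rescue SMI, because the DXA rule selects paired SMI under any grouping.

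A reader might infer that the SMI comparison is impossible. The documents do not support that. Men diagnosed at T0, and probable cases with SMI of 7.0 or more, have a T0 scan, and some will have a second. The comparison can be computed, but only in a small and selected subset.

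A reader might also size the handgrip bias by splitting at 27 kg alone. With the same mean and SD, z = (27 − 30)/8 = −0.375. The group means then lie 8 × 0.372/0.354 = 8.41 kg below and 8 × 0.372/0.646 = 4.60 kg above the overall mean, so the spurious difference is 13.0 × (1 − r): 1.3 kg at r = 0.9 and 2.6 kg at r = 0.8. This overstates it. Sarcopenia also requires SARC-F and SMI, which leaves some low-grip men in the comparison group, and step 5 of the working gives 0.7 to 0.9 and 1.4 to 1.8 kg. Men admitted on chair stand alone would dilute the handgrip effect further.

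Finally, the contested test is not the only analysis. The same section compares secondary endpoints across all patients between the two assessments and plans multivariable regression. That limits the damage, but does not make this test interpretable.

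**Conclusion.** The concern holds in two parts of different strength. From the text alone, SMI change is observed only in men who meet the DXA rule at both visits, so any between-group test of it rests on a subset selected on the outcome. If the groups are sarcopenic versus not, the handgrip and chair-stand comparisons are distorted as well: by regression to the mean with T0 groups, and by construction with T1 groups. Repeated-measures ANOVA corrects neither.

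For handgrip with T0 groups the size is roughly 0.7 to 2.7 kg, for T0–T1 correlations of 0.9 to 0.7. The figures are illustrative and rest on assumed distributions; the mechanism and direction do not depend on their exact values. The chair-stand effect was not sized. A reader might carry the problem over to the primary endpoint, but T0 prevalence uses no change score and no group comparison, and it is not affected.

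**What to change.** 1. Drop the between-group test of SMI change. Report SMI change descriptively in patients scanned at both visits, give their number, and label them as selected by the DXA rule.
2. Replace the two-group ANOVA for handgrip and chair stand by a regression of the T1 value on the continuous T0 value. Use exposures that are already collected and not built from the outcome, for example ADT duration (from the recorded treatment dates), age, MNA and physical activity.
3. Reconcile the Screening and enrollment and Primary endpoint sections with Table 1 on who has strength testing. If testing is restricted to patients with an impaired SARC-F, state that the regression applies only to tested patients.

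Items 1 and 2 change analysis wording only and need no added scan or visit. Item 3 is also wording, but its outcome decides how much of the cohort the regression can cover.

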### Statistical considerations

#### Sample size, power, and statistical methods

Under the assumption that the prevalence of sarcopenia in older patients with prostate cancer before initiation of treatment with ADT is between 20 to 30%, according to one of the rare studies published on the subject [21], a sample size of 200 subjects allows an estimation with a width of two-sided 95% confidence interval between 0,115 to 0.131. Previous feasibility analysis showed current collaboration between urologist, radiotherapist and geriatrician should allow enrollment of the adequate number of patients during the trial period.

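### Linear regression is named for sarcopenia occurrence, a yes/no outcome; a binary-outcome model should replace it and the covariate-selection sentence should be made clear

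*Protocol article*

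**What the plan says.** The Data analysis section gives one multivariable method for the factors associated with sarcopenia: "Multivariate analysis using linear regression models will be performed to determine the association between our analyzed variables and sarcopenia occurrence". The next sentence deals with covariates: "Variables relevant to the models will be selected based on their clinical significance (two-tailed with 5% significance level".

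The outcome is a status set by a threshold. The Primary endpoint section states: "Chosen cut-off point for low SMI indicating sarcopenia diagnosis as per EWGSOP2 guidelines is <7.0 kg/m2". Data analysis applies the same threshold at both visits: an SMI under 7 kg/m² "at enrollment and /or a year after ADT end is considered as a proven sarcopenia diagnosis". SMI is not measured in everyone: "Only patients with probable sarcopenia (SARC-F score ≥4/10 and then muscle strength impairment), will benefit from a DXA exam".

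The sample-size section assumes that prevalence "before initiation of treatment with ADT is between 20 to 30" per cent and reports that "a sample size of 200 subjects allows an estimation with a width of two-sided 95% confidence interval between 0,115 to 0.131". It gives no figure for incidence at T1 (one year after ADT ends), for effect sizes or for the precision of the regression.

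The Abstract names risk factors for prevalence and the relation of ADT to incidence as primary objectives. The Endpoints section makes prevalence at T0 (enrolment) the primary endpoint and lists the factor and ADT analyses as secondary.

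**The concern.** Ordinary linear regression assumes an error variance that does not depend on the covariates. For a 0/1 outcome the variance is p(1 − p), so it changes whenever the risk changes. The pooled standard error is then wrong for any factor that has an effect and splits the cohort unevenly, and fitted risks can be negative or exceed 1.

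This is a method that the article states, so it is not a detail left to a fuller document. The other methods in the section do not cover the need. The chi-square, Fisher and t tests compare the two assessments, and the repeated-measures analysis of variance compares changes in scores. None of them gives adjusted associations with sarcopenia. At stake are the intervals and tests for the risk factors and the ADT–incidence relation, which are meant to inform prevention.

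The selection sentence adds a second difficulty. It names clinical significance as the criterion and attaches a 5% two-tailed level, so a reader cannot tell whether covariates are chosen by judgement or by p-value.

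**Working it through.** **The plan's own figure.** Exact (Clopper-Pearson) 95% intervals at n = 200:
- 40/200 gives 0.1469 to 0.2622, width 0.1153.
- 60/200 gives 0.2374 to 0.3686, width 0.1313.

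These match the stated 0.115 and 0.131. The prevalence calculation is sound and involves no regression.

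**Could the outcome be continuous SMI?** The sentence says occurrence. DXA is also restricted to patients with SARC-F ≥4 and impaired strength, so patients outside that group have no SMI value. A linear model for SMI could not be fitted to the whole cohort.

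**Size at T0, two-group formula.** Inputs from the protocol: n = 200 and overall risk 20% or 30%. Assumed: 10% exposed (n₁ = 20, n₀ = 180) and odds ratios of 2 and 4.
- OLS variance = s² × (1/n₁ + 1/n₀), where s² = [n₁p₁(1 − p₁) + n₀p₀(1 − p₀)]/n
- True variance = p₁(1 − p₁)/n₁ + p₀(1 − p₀)/n₀
- R = √(true/OLS); coverage = 1 − 2Φ(−1.96/R)

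Example, overall risk 20% and odds ratio 4 (p₀ = 0.1718, p₁ = 0.4535): s² = 0.1529. OLS variance = 0.1529 × (1/20 + 1/180) = 0.00849. True variance = 0.01239 + 0.00079 = 0.01318. R = 1.25 and coverage is 88.4%.

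| Overall risk | Odds ratio | p₀ | p₁ | OLS variance | True variance | R | Coverage |
|---|---|---|---|---|---|---|---|
| 20% | 2 | 0.1872 | 0.3153 | 0.00881 | 0.01164 | 1.15 | 91.2% |
| 30% | 2 | 0.2842 | 0.4426 | 0.01154 | 0.01347 | 1.08 | 93.0% |
| 20% | 4 | 0.1718 | 0.4535 | 0.00849 | 0.01318 | 1.25 | 88.4% |
| 30% | 4 | 0.2674 | 0.5935 | 0.01113 | 0.01315 | 1.09 | 92.9% |

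With 50% exposed, coverage is 95% in all four cases. With 70% exposed it is 96 to 98%, which is conservative. With an odds ratio of 1 it is 95%.

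**Size with several covariates, simulation.** Each scenario had 1,000 data sets with one binary factor (15% exposed) and two standard normal factors. The figures are coverage for the binary factor across odds ratios 1, 2 and 4.

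| Setting | OLS, odds ratio 1 | OLS, odds ratio 2 | OLS, odds ratio 4 | OLS with robust (HC3) errors | Logistic |
|---|---|---|---|---|---|
| n = 200, risk 20–30% | 95% | 93–94% | 91–92% | 94–96% | 94–96% |
| n = 150, risk 5–10% | 95–96% | 89% | 81–84% | 77–93% | 96–98% |

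The second row stands for new cases at T1. Its event rates are assumptions. Its n is close to 200 × 0.70 = 140 to 200 × 0.80 = 160, the number free of sarcopenia at T0 if nobody drops out.

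The OLS coefficient equalled the true marginal risk difference at T0 (0.122 against 0.122; 0.247 against 0.247). Where factors had effects at T0, 0.4 to 4.9% of patients had fitted risks outside 0 to 1. In the rarer-event settings this reached 14.5%.

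**Selection sentence.** Cases expected at T0: 200 × 0.20 = 40 to 200 × 0.30 = 60. At an assumed 10 cases per model term, this supports 4 to 6 terms. The secondary endpoints list about 15 socio-behavioural and geriatric items, one of which is gender, a constant in this all-male cohort. If the 5% level were a univariate screen, the chance of keeping at least one of 11 unrelated factors would be 1 − 0.95¹¹ = 43% (40 to 45% in 500 simulated data sets). A true log-odds ratio of 0.40 would then average 0.49 to 0.53 when retained. These figures apply only on that reading.

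**The case against.** The best defence is that a linear model for a 0/1 outcome is a recognised way to estimate risk differences. That stands: the estimates are not biased for the marginal difference, there is no loss of coverage when a factor has no effect, and at T0 the shortfall for plausible effects is a few percentage points. The objective is association, so out-of-range fitted risks matter less than they would for prediction. The defence is incomplete because the article specifies neither a risk-difference analysis nor robust standard errors, and because the shortfall grows as cases become rarer.

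A reader might infer that the risk-factor estimates and intervals are simply invalid. The figures do not support that. Coverage near 81% can be produced at n = 200, for example with 10% exposed and risks of 50% against 10%. That example has an overall risk of 0.1 × 50% + 0.9 × 10% = 14%, below the planned range, and an odds ratio of 9. It does not describe the T0 analysis.

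A reader might also infer that covariates will be screened at p < 0.05. The sentence names clinical significance as the criterion, and the parenthesis may only give the test level. What stands is that the wording is ambiguous. A full covariate list can reasonably be left to an analysis plan.

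**Conclusion.** The point holds as a wrong model class for a binary outcome, stated in the article and not rescued by any other method there. It should be fixed, but it does not threaten the trial's main result. The T0 prevalence estimate, its interval and the sample of 200 need no regression.

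At T0, nominal 95% intervals for an uncommon factor cover about 91 to 94% at an odds ratio of 2 and 88 to 93% at 4. They are nominal with no effect and can be conservative for common exposures. For new cases at T1, coverage can fall to about 81 to 89% when the factor has an effect. Exposure shares, odds ratios, the T1 event rates and n = 150 are assumptions, since the protocol gives none. Only the 200 patients and the 20 to 30% prevalence come from it.

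The selection sentence is unclear. It is not shown to be a p-value rule.

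**What to change.** Replace linear regression for sarcopenia occurrence with a binary-outcome model, fitted separately for sarcopenia at T0 and for new sarcopenia at T1 among patients free of it at T0. Either of these would serve:
- logistic regression, penalised if cases are few; or
- a risk-difference or risk-ratio model with robust standard errors.

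The second option suits T0. With few cases at T1, robust errors on the linear model covered only 77 to 93% in the simulation above, so logistic regression is safer there. Keep linear models for continuous outcomes such as handgrip strength and gait speed.

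Reword the selection sentence so that covariates are chosen beforehand on clinical grounds, in a number that about 40 to 60 cases can support at T0 (4 to 6 terms at 10 cases per term) and fewer at T1 if new cases are fewer. Say that the 5% two-tailed level applies to testing only.

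The cost is analysis wording. Design, sample size and data collection do not change. The named software fits standard logistic models; a penalised fit needs an add-on or other free software.

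### Categorical endpoints measured twice on the same men are to be compared with chi-square or Fisher's exact test, which ignore the pairing and lose power

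*Protocol article*

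**What the plan says.** All places are in the protocol article.

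- **Same men twice.** Under Follow-up – T1, a year after treatment ends, "patient will once again benefit from CGA and sarcopenia assessment as described for T0".
- **Tests between T0 and T1.** Under Data analysis: "The secondary endpoints will be compared for all the patients between the 2 assessments (Chi2 test or" Fisher's exact test, where the variable is categorical, with "Student’s t test for continuous variables".
- **Repeated-measures method.** The same section says that "the analysis of variance for repeated measurements will be performed to compare the changes in the scores over time between the 2 groups". This concerns changes in SMI, handgrip strength and chair stand.
- **Incidence.** The first secondary endpoint is "The evaluation of sarcopenia incidence in patients 70 years and older with localized or locally advanced prostate cancer a year after the end of ADT". Its analysis is described in one sentence: "To evaluate incidence, enrollment (T0) will be considered as baseline and compared to T1 data".

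The section names no paired test for a binary outcome and states no at-risk set for incidence.

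**The concern.** Chi-square and Fisher's exact test compare proportions in two independent samples. To apply them here, each man is entered once in the T0 row and once in the T1 row, and the link between his two results is thrown away. A man's sarcopenia status or other categorical geriatric finding at T0 is likely to resemble his own at T1. The variance that the test uses is then too large, and a real worsening after androgen deprivation therapy (ADT) is more easily missed.

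This matters because change after ADT is one of the study's two stated aims, and the Abstract lists the relation between ADT and sarcopenia incidence among the primary objectives. A missed change would weigh wrongly against the prevention programmes that the Discussion has in view.

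A second, smaller point follows. A comparison of all patients at T1 with all patients at T0 measures new cases minus resolved cases. That is a different quantity from incidence.

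**Working it through.** **The plan's own figure.** For N = 200 the plan gives a 95% interval width of 0.115 to 0.131 at prevalences of 20% to 30%. The exact binomial (Clopper-Pearson) interval reproduces this: 40/200 gives 0.1469 to 0.2622, width 0.1153; 60/200 gives 0.2374 to 0.3686, width 0.1313. The figure concerns T0 prevalence only, so the pairing does not touch it.

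**Inputs for the T0–T1 comparison.** From the plan: N = 200, a two-sided 5% level (given where model variables are selected), and T0 prevalence of 20% to 30%, here 25%. Assumed, because the plan gives no value: 35% at T1, complete pairs, and a within-patient (phi) correlation ρ of 0.3, 0.5 or 0.7.

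**Type I error, 25% at both times.** The chi-square standard error is too large by a factor 1/√(1−ρ), so the true size is approximately 2Φ(−1.96/√(1−ρ)):

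- ρ = 0.3: 2Φ(−2.34) = 1.9%
- ρ = 0.5: 2Φ(−2.77) = 0.56%
- ρ = 0.7: 2Φ(−3.58) = 0.035%

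A simulation with 20,000 replicates gives 1.9%, 0.6% and 0.04%. McNemar's test stays at about 5% in each case.

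**Cell probabilities for 25% to 35%.** The probability of sarcopenia at both times is p11 = 0.25 × 0.35 + ρ√(0.1875 × 0.2275) = 0.0875 + 0.2065ρ. New cases are p01 = 0.35 − p11 and resolved cases are p10 = 0.25 − p11.

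**Test statistics at the expected values.** Chi-square: z = 0.10/√(2 × 0.30 × 0.70/200) = 2.18 whatever ρ is. McNemar: z = 0.10/√((p01 + p10)/200).

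| ρ | p11 | p01 | p10 | McNemar z | Power, chi-square | Power, McNemar |
|---|---|---|---|---|---|---|
| 0.3 | 0.149 | 0.201 | 0.101 | 2.58 | 60% | 74% |
| 0.5 | 0.191 | 0.159 | 0.059 | 3.03 | 62% | 87% |
| 0.7 | 0.232 | 0.118 | 0.018 | 3.84 | 66% | 99% |

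Powers are simulated. At ρ = 0 both tests have 58%. If only 150 pairs were complete (assumed), the powers at ρ = 0.3, 0.5 and 0.7 would be 47%, 47% and 45% for chi-square and 62%, 77% and 96% for McNemar.

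**Net change against incidence.** In all three rows the net change is 10 points. Incidence among men free of sarcopenia at T0 is p01/0.75, that is 26.7%, 21.2% and 15.7%. In an extreme assumed case, with 20% incidence and 60% resolution, new cases are 0.75 × 0.20 = 0.15 and resolved cases are 0.25 × 0.60 = 0.15, so the net change is zero. The at-risk set would be about 140 to 160 of 200 men (T0 prevalence 30% to 20%), before any loss to follow-up.

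**The case against.** **The t test may be paired.** A paired t test is a Student's t test, and the text never says that the samples are independent. A reader might infer that continuous endpoints are also analysed wrongly. The document does not support that; it leaves the form open. This objection stands, and the continuous limb is a request for one word of clarification.

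**The plan does use a repeated-measures method.** It names repeated-measures analysis of variance for score changes, so its authors saw the dependence between the two visits. That is fair for SMI, handgrip and chair stand. But the method is tied to a contrast between two groups. It covers neither binary sarcopenia status nor the comparison of all patients between visits.

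**Incidence may be intended correctly.** A reader might infer that incidence will be computed by subtracting two prevalences. The incidence sentence names no test and no denominator, and counting new cases against baseline status fits it equally well. The reference to all patients sits in a later sentence about the secondary endpoints as a group, and all patients is the natural set for mobility and quality of life. The objection stands as far as it goes: the document does not prescribe the wrong calculation. It does not exclude it either.

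**The direction is safe.** With positive correlation the error produces no excess of false positives. That is true, but lost power is a real cost in a study meant to detect worsening.

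**A reversal of significance is not shown.** With 150 pairs the expected chi-square result for 25% to 35% is z = 1.89, p = 0.059, and a reader might infer that the planned test would miss what a paired test finds. At the stated N = 200 it is z = 2.18, p = 0.029, so both tests are significant at the expected values. The supportable claim is about size and power over a range.

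**Conclusion.** For categorical endpoints the plan is wrong as written: it prescribes tests for independent samples on paired data. The test is conservative, with a true size of about 1.9% down to 0.04% in place of 5%, and a loss of roughly 13 to 33 percentage points of power against McNemar's test (74 − 60 = 14, 87 − 62 = 25, 99 − 66 = 33 from the rounded powers). These sizes rest on assumed correlations of 0.3 to 0.7, 200 complete pairs and an assumed change from 25% to 35%. The mismatch between test and design needs none of these assumptions, although without correlation it would do no harm. The primary T0 prevalence estimate and its sample size are unaffected. The t test and the incidence denominator are points to clarify.

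**What to change.** In Data analysis:

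1. For categorical T0–T1 comparisons, replace chi-square and Fisher's exact test with McNemar's test, in its exact form if discordant pairs are few, and report a paired confidence interval for the change.
2. State that the t test is paired, with the Wilcoxon signed-rank test as the alternative.
3. Define incidence as new confirmed sarcopenia at T1 among patients assessed at T1 and free of sarcopenia at T0, with an exact 95% confidence interval.

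The cost is a few sentences. No further data, visits or patients are needed. The Trial status section gives the study as recruiting, so at that stage the change could be made before the T1 analysis.
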